### Randomization and blinding

Medical students will enroll in the study in teams of two based on schedule availability, without matching for prior teamwork experience, clinical rotation level, or other characteristics. Each team will be treated as a cluster and randomly allocated to the self-guided or facilitator-guided group at a 1:1 allocation ratio.

The principal investigator will generate the randomization sequence using Sealed Envelope’s online randomization service [56]. Upon participant enrolment, the principal investigator will assign each team a team-ID based on the order of enrolment and allocate teams to interventions according to the randomization sequence.

The raters assessing the pretest and posttest videos will be blinded to group allocation. Due to the nature of the interventions, blinding of participants is not feasible. However, participants will not be informed of their group allocation until the intervention day, after completing the pretest, the VR scenarios used for intervention delivery are pre-programmed and identical across the intervention groups to ensure standardization, and the performance evaluation scenarios will follow standardized protocols. The researchers doing the statistical analyses will be blinded to allocation of participants.

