**Research question 2 (RQ2 – effect on overall team performance)**

Do the two interventions result in a similar effect on medical students’ technical team performance (ABCDE adherence and time to critical actions)? (RQ2a)

Does VR improve overall team performance (teamwork skills, ABCDE adherence, and time to critical actions) in both intervention groups? (RQ2b)

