### Outcome measures

Outcome measures and assessment tools are further described in Table 1.

**Table 1 pone.0332309.t001:** Assessment tools, research hypothesis, and outcome measures.

	Assessment tool	Research question	Outcome measure
Team-level outcome (n = 22 teams in each arm)	**Primary outcome**		
	**Clinical Teamwork Scale (CTS®)** [45] − 15 teamwork skills in five main domains: overall teamwork, communication, situational awareness, decision-making − 11-point Likert scale ranging from 1 = unacceptable to 11 = perfect	RQ1: Is the change from pretest to posttest in the self-guided group non-inferior compared to the facilitator-guided group, with a non-inferiority margin of 0.5? RQ3: Is there a significant increase from pretest to posttest in both groups?	Mean CTS score (mean across 15 items and across the two raters.)

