### Data collection and management

Participant recruitment will take place from May 6^th^, 2025, to October 31^st^, 2025. Data collection began on May 6^th^, 2025, and is expected to be completed by November 2025. Results are anticipated by June 2026. Schedule of enrolment, interventions, and assessments is presented in Fig 1.

Teams will be assessed before the intervention managing a mannequin-based pediatric emergency (pretest) and again after the intervention (posttest). The mannequin-based simulation will be video recorded and two independent, blinded raters will rate team performance based on the videos. Teams will be randomly assigned one case at pretest and complete the other at posttest. Scenarios will be recorded using a GoPro HERO 4 camera. The raters will be a medical doctor and a medical student, both trained and experienced in assessing team performance using these instruments.

Additionally, after the intervention all participants will complete questionnaires on perceived debriefing quality, motivation, workload, cybersickness, and usability (Table 1 and Fig 1).

Pretest and posttest videos will be stored on a secure hospital drive as logged files, accessible to only to authorized study personnel and are permanently deleted after completion of analyses. All other data will be stored in a secure online database (REDCap) [54] and be pseudonymized before imported into R (version 4.1.2) for statistical analysis [55].

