### Statistical analysis

We will report descriptive statistics on baseline characteristics of each group, reporting continuous variables using median and interquartile range and categorical variables as n/total N (%). Descriptive statistics will be reported for all outcomes at each time point as mean, standard deviations, median, and interquartile range.

We will analyze the team-level data (RQ1 and RQ2) using a constrained linear mixed model with inherent baseline adjustment. Visit (pretest or posttest), assessment scenario (pneumonia or asthma), and the constrained interaction between visit and treatment group (self-guided vs facilitator-guided) will be included as fixed effects. An unstructured covariance pattern will be applied to account for the correlation between repeated measurements and potential changes in variance over time and account for missing data. The mean between the two raters will be calculated prior to statistical analysis.

To analyze individual-level outcomes (RQ3 and RQ4), we will apply a constrained linear mixed model with treatment group as fixed effect and a blocked compound symmetry pattern to account for intra-class correlation between individuals in the same team.

Missing data will be handled within the linear mixed model under the assumption that data are missing at random by including all available data points without requiring imputation. For missing individual-level covariate or questionnaire data, we will first assess the extent and pattern of missingness. If missingness exceeds a minimal threshold of >5%, we will apply multiple imputation using chained equations to account for missing values [57].

For the primary outcome (RQ1), we will report point estimates and two-sided 95% CI. Non-inferiority will be concluded, and the null hypothesis rejected, if the lower bound of the CI exceeds the negative non-inferiority margin [58,59].

For secondary outcomes (RQ2, RQ3, and RQ4), we will report point estimates, two-sided 95% CI, and p-values, and the null hypothesis will be rejected if p < 0.05. RQ5 related outcomes will be reported descriptively using median and interquartile range.

We will adjust for multiple testing using the Holm method to control the family-wise error rate within each family of research questions, except for the primary outcome [58,60].

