Fourth, randomization was performed at the team (cluster) level without stratification for potential confounding variables (e.g., prior VR or simulation experience), and team composition was not matched for, e.g., prior teamwork experience or clinical rotation level, which may introduce variability in baseline teamwork performance between groups. While baseline characteristics will be compared between groups, chance imbalances cannot be entirely excluded. Fifth, repeated testing introduces the risk of carryover or practice effects. Although scenarios differ in content but are matched for complexity, repeated exposure may lead to learning independent of the intervention. However, this is likely to affect both groups equally, potentially exaggerating overall improvements but not the primary non-inferiority comparison. Finally, although self-guided debriefing will be supported by standardized prompts to ensure consistency, there remains a possibility of variability in the depth and quality of reflection achieved between individuals and teams. These factors should be considered when interpreting the results.

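### RQ2b asks whether VR improves team performance, but within-arm pre-post tests with no untrained arm, and no stated masking of raters to visit, cannot answer it

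*Protocol article*

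**What the plan says.** All places are in the protocol article.

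- **Question.** Research question 2 asks under RQ2b: "Does VR improve overall team performance (teamwork skills, ABCDE adherence, and time to critical actions) in both intervention groups". The wording is causal and VR is its subject.
- **Test.** Table 1 (Outcome measures) turns this, for CTS, the ABCDE checklist and time to critical actions, into "Is there a significant increase from pretest to posttest in both groups". The table numbers these entries RQ3, but they match RQ2b of the text.
- **Decision rule.** Statistical analysis states for the secondary outcomes that "the null hypothesis will be rejected if p < 0.05", and adds: "We will adjust for multiple testing using the Holm method to control the family-wise error rate within each family of research questions".
- **Arms.** Under Study design, both randomised arms go through the VR training and differ in how the debriefing is led. No arm goes untrained.
- **Timing.** The Fig 1 legend puts pretest, intervention and posttest on one day.
- **Rater blinding.** Randomization and blinding states: "The raters assessing the pretest and posttest videos will be blinded to group allocation". The abstract, Study design and the RQ1 and RQ2 outcome sections give the same scope. Data collection and management and the ethics section mention blinding without giving its scope.
- **Case order.** "Teams will be randomly assigned one case at pretest and complete the other at posttest". Assessment scenario is a fixed effect in the model.
- **Conceded limitation.** Strengths and limitations says that "repeated exposure may lead to learning independent of the intervention" and that this could overstate overall improvement without affecting the primary comparison.

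**The concern.** A within-arm change from morning to afternoon is the sum of everything that happened in between. Part of it is the effect of VR training with debriefing. Part may be learning from the first mannequin test and growing familiarity with the mannequin and the teammate. Part may be higher scoring by a rater who knows or guesses that a video is a posttest. Every team has the intervention between its two visits, so visit and exposure coincide completely and no model term can separate these parts.

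The limitations section accepts that retesting may exaggerate overall improvement, and that is the quantity RQ2b tests. The question, its test and its decision rule nevertheless stay as they are. Rater expectation is not discussed. Blinding to arm protects RQ1 and RQ2a, but it does nothing for a contrast between visits.

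At stake is a secondary conclusion that VR improves team performance when part or all of the change has another source.

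**Working it through.** **1. The plan's own figure.** The article gives no power for RQ2b. Its only calculation is for the primary outcome: margin 0.5, SD 0.63, one-sided alpha 0.05, power 80%.

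n per arm = 2 × (1.645 + 0.842)² × 0.63² / 0.5² = 19.6, rounded up to 20 teams.

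This matches the 20 teams stated. Table 1 plans 22 teams per arm.

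**2. Inputs for the illustration.**
- Teams per arm: 22 (Table 1).
- SD of the pretest-to-posttest change: 0.63, an assumption. Sample size calculation does not say whether its 0.63 refers to a score or to a change. The range used is 0.5 to 0.9.
- True intervention effect: zero, an assumption.
- Shift from retesting or rating, shared by both arms: 0.4 CTS points, an assumption. The documents give no value.
- A two-sided paired t-test stands in for the constrained mixed model, so the results are approximate.

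**3. How large an observed change must be.**

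SE = 0.63 / √22 = 0.134. With 21 degrees of freedom the critical t is 2.080 at 0.05, so an observed change above 2.080 × 0.134 = 0.28 points is significant. For SD 0.5 the limit is 0.22, and for SD 0.9 it is 0.40.

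If the six within-arm tests (three outcomes × two arms) form one Holm family, the first step is 0.05/6 = 0.0083. The critical t is then 2.912 and the limit is 0.39 points at SD 0.63.

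**4. Probability of a significant increase in one arm when the true shift is 0.4 and none of it comes from the intervention.**

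Noncentrality = 0.4 / SE, which is 0.4 / 0.134 = 2.98 at SD 0.63. From the noncentral t distribution with 21 degrees of freedom:

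| SD of change | at p < 0.05 | at 0.05/6 |
|---|---|---|
| 0.5 | 0.95 | 0.79 |
| 0.63 | 0.81 | 0.54 |
| 0.9 | 0.51 | 0.24 |

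With SD 0.63, a true shift of 0.3 gives 0.57 at p < 0.05 and 0.28 at 0.05/6. A true shift of 0.5, the size of the non-inferiority margin, gives 0.94 and 0.78.

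**5. What Holm can and cannot do.** Holm limits false rejections when null hypotheses are true. Here the null of no change is false because of the shift; the error lies in attributing the change to VR. A stricter threshold makes that error rarer but does not remove it.

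**6. Between-arm comparisons.** If both arms carry the same shift s, the difference in change is (effect A + s) − (effect B + s) = effect A − effect B. The shift cancels.

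**The case against.** The strongest reply is that the article already discloses the problem and limits its consequence to overall improvement. It uses distinct, matched scenarios, randomises case order and adjusts for scenario. This stands in part. Case difficulty is handled, and the case does not reveal the visit. But a disclosed bias does not turn a within-arm test into an answer to a question about the effect of VR, and rater expectation is not disclosed.

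Three stronger readings are tempting and are not supported.

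- **A reader might infer that raters know which video is the posttest.** No section says so. Some mentions of blinding give no scope, and a condensed article may leave file coding and rating order to the full protocol. All that can be said is that masking to visit is not stated and that the stated scope does not cover RQ2b.
- **A reader might count debriefing as a confounder.** The Interventions section makes it part of both interventions. Only retesting and rating remain as rival explanations.
- **A reader might charge RQ2b with a large power cost to RQ2a through a shared Holm family.** With eight tests the first step is 0.05/8 = 0.00625. Power for a 0.8 SD between-arm difference at that level is 42%, against 63% at 0.025. But Holm steps down as tests are rejected. In a simulation with independent tests, a second between-arm comparison that is null, and SD of change 0.63, power is 63% in both the eight-test and the two-test family when the within-arm change is 1.2 points (the pilot's facilitator-guided CTS change). It is 58% against 63% at 0.5 points. The 42% arises only if the within-arm tests show essentially no effect, and the article does not fix whether the family is shared.

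It would also be wrong to call a 0.3-point shift simply significant. That confuses an observed change with a true one and ignores Holm.

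**Conclusion.** The point holds in limited form. RQ2b is a causal question about VR, tested by uncontrolled change within each arm. Followed as written, the plan could credit VR with a practice or rating shift. With no intervention effect, a shared shift of 0.4 CTS points would give a significant increase in one arm with probability 0.81 at p < 0.05 (0.51 to 0.95 for SD 0.9 to 0.5), or 0.54 at 0.05/6. These figures rest on an assumed shift and an assumed SD of change. They show what the test would do with such a shift, not that one will occur.

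The point is confined to a secondary question. RQ1 and the other between-arm comparisons are largely protected as long as the shift is the same in both arms.

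**What to change.** 1. Reword RQ2b and the matching Table 1 entries as change from pretest to posttest in each arm. Report estimates with 95% CIs and draw no conclusion that VR caused the change.
2. Give each video a random code without date or visit label, shuffle pretest and posttest videos across teams, and state that raters score them masked to visit as well as arm. Randomised case order makes this feasible.
3. For videos already rated, disclose whether the visit was masked.

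The cost is renaming and shuffling files plus a few changed lines. The downside is that a headline that VR improves performance is given up.

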### Statistical analysis

We will report descriptive statistics on baseline characteristics of each group, reporting continuous variables using median and interquartile range and categorical variables as n/total N (%). Descriptive statistics will be reported for all outcomes at each time point as mean, standard deviations, median, and interquartile range.

We will analyze the team-level data (RQ1 and RQ2) using a constrained linear mixed model with inherent baseline adjustment. Visit (pretest or posttest), assessment scenario (pneumonia or asthma), and the constrained interaction between visit and treatment group (self-guided vs facilitator-guided) will be included as fixed effects. An unstructured covariance pattern will be applied to account for the correlation between repeated measurements and potential changes in variance over time and account for missing data. The mean between the two raters will be calculated prior to statistical analysis.

To analyze individual-level outcomes (RQ3 and RQ4), we will apply a constrained linear mixed model with treatment group as fixed effect and a blocked compound symmetry pattern to account for intra-class correlation between individuals in the same team.

Missing data will be handled within the linear mixed model under the assumption that data are missing at random by including all available data points without requiring imputation. For missing individual-level covariate or questionnaire data, we will first assess the extent and pattern of missingness. If missingness exceeds a minimal threshold of >5%, we will apply multiple imputation using chained equations to account for missing values [57].

For the primary outcome (RQ1), we will report point estimates and two-sided 95% CI. Non-inferiority will be concluded, and the null hypothesis rejected, if the lower bound of the CI exceeds the negative non-inferiority margin [58,59].

For secondary outcomes (RQ2, RQ3, and RQ4), we will report point estimates, two-sided 95% CI, and p-values, and the null hypothesis will be rejected if p < 0.05. RQ5 related outcomes will be reported descriptively using median and interquartile range.

We will adjust for multiple testing using the Holm method to control the family-wise error rate within each family of research questions, except for the primary outcome [58,60].

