## Methods

### Setting and population

The study will be conducted at Copenhagen University Hospital, Rigshospitalet, and Odense University Hospital, Denmark. Eligible participants will be medical students enrolled at Faculty of Health and Medical Sciences, Copenhagen University and University of Southern Denmark, who are within two years of graduation. Exclusion criteria will be lack of informed consent.

Participants will be recruited between May and October 2025 via emails sent to the consultants responsible for medical students’ clinical placements at pediatric departments in the Capital Region of Denmark, Region Zealand, and the Region of Southern Denmark. These consultants will be encouraged to inform medical students, both in person and via email, about the opportunity to participate in the study. Additionally, information and invitations to participate will be shared on social media platforms targeting medical students in the relevant regions. Written informed consent, including permission to record and store all video data for the research project, will be obtained from all participants upon enrolment.

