**Fig 2 pone.0332309.g002:**
[figure not shown]
Illustration of pretest, posttest, and intervention phases. The self-guided group will receive a debriefing script based on the Promoting Excellence And Reflective Learning in Simulation (PEARLS) framework [43] adapted for VR and self-guided use [30,44]. No facilitator will be present, but participants may request technical support. A research assistant will introduce the VR simulation, administer questionnaires, and confirm that all scenarios and debriefings were completed.

In the facilitator-guided group, a medical doctor with formal training and experience in simulation and debriefing will guide the debriefings using the same VR-modified PEARLS framework as the self-guided group. This ensures that the only planned difference between groups is the presence or absence of a facilitator [30,43].

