### Sample size calculation

The sample size calculation is based on the assumption that self-guided debriefing is non-inferior to facilitator-guided debriefing for the primary outcome (teamwork skills measured by the CTS© scale.) We set a non-inferiority margin of 0.5 points on the 0–10 CTS© scale, meaning that a difference of less than 0.5 points on the CTS© scale is not expected to constitute a meaningful difference in teamwork skills. The non-inferiority margin was informed by expert consensus, our experience rating teamwork skills in the pilot study, and pilot data [30]. Based on a one-sided two-sample t-test with a non-inferiority margin of 0.5, an alpha of 0.05, a power of 80%, and a standard deviation of 0.63 derived from our pilot data [30], the required sample size is 20 teams (40 participants) in each arm. Assuming a 10% dropout rate, we plan to include approximately 44 participants in each arm, and 88 participants in total. The sample size calculation was performed in R version 4.1.2 [55].

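### The primary model has no site or facilitator term: leaving out site costs a little precision, and ignoring shared facilitators makes the non-inferiority interval too narrow if facilitators differ

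*Protocol article*

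**What the plan says.** All references are to the protocol article.

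- **Model (Statistical analysis).** The fixed effects for the team-level outcomes are listed in full: "Visit (pretest or posttest), assessment scenario (pneumonia or asthma), and the constrained interaction between visit and treatment group (self-guided vs facilitator-guided) will be included". The covariance is unstructured over a team's pretest and posttest. The individual-level model has treatment group as its fixed effect and allows for correlation within a team. Neither model has a site or facilitator term.
- **Decision rule (Statistical analysis).** Non-inferiority is concluded if the lower limit of the two-sided 95% interval lies above −0.5, which is a one-sided error of 2.5%.
- **Sites (Setting and population).** "The study will be conducted at Copenhagen University Hospital, Rigshospitalet, and Odense University Hospital, Denmark". Students come from two universities. Strengths and limitations states that randomization was not stratified.
- **Facilitators (Interventions, text with Fig 2).** In one arm "a medical doctor with formal training and experience in simulation and debriefing will guide the debriefings"; in the other no facilitator is present. The article does not say how many doctors do this, at which site, or for how many teams each.
- **Size (Sample size calculation).** With "a standard deviation of 0.63 derived from our pilot data" and a margin of 0.5, "the required sample size is 20 teams (40 participants) in each arm"; 22 teams per arm are planned.

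**The concern.** The list of terms treats all 44 teams as independent. For the facilitator-guided arm this is doubtful. Unless 22 different trained doctors take part, some teams share a debriefer, and their posttest scores can share whatever that doctor adds or fails to add. The self-guided arm has no such shared source. This is a partially nested design: clustering above the team exists in one arm only. The plan recognises clustering at team level but stops there.

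The direction matters. Non-inferiority is declared from the lower limit of the interval, so an interval that is too narrow favours declaring it. The facilitator is also the one planned difference between the arms, and the Discussion speaks of facilitator-guided debriefing in general, not of particular doctors.

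Site is a different matter. Two hospitals and two student populations, without stratification, can leave the arms with a different site mix by chance. The price is precision, not validity.

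**Working it through.** **Inputs from the article:** margin 0.5; SD 0.63; 22 teams per arm planned; two-sided 95% interval; two sites. **Assumptions, because the article does not give them:** number of facilitators k, facilitator ICC, an even split of sites, a site difference of 0.3 points, and the pretest–posttest correlation.

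**Step 1. The plan's own figure.** n = 2 × (1.645 + 0.842)² × 0.63² / 0.5² = 19.6, so 20 teams per arm. The stated figure reproduces. It assumes independent teams.

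**Step 2. Facilitators.** With m = 22/k teams per facilitator, the design effect in the facilitator-guided arm is DE = 1 + (m − 1) × ICC; in the self-guided arm it is 1. The true standard error exceeds the planned one by r = √((1 + DE)/2). The one-sided error at the margin is 1 − Φ(1.96/r). The planned half-width is 1.96 × 0.63 × √(2/22) = 0.372, and the correct one is 0.372 × r.

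| k | m | ICC | DE | r | Correct half-width | One-sided error | Coverage of planned 95% interval |
|---|---|---|---|---|---|---|---|
| any | – | 0 | 1.00 | 1.000 | 0.372 | 0.025 | 95.0% |
| 2 | 11 | 0.01 | 1.10 | 1.025 | 0.381 | 0.028 | 94.4% |
| 2 | 11 | 0.05 | 1.50 | 1.118 | 0.416 | 0.040 | 92.0% |
| 2 | 11 | 0.10 | 2.00 | 1.225 | 0.456 | 0.055 | 89.0% |
| 4 | 5.5 | 0.05 | 1.23 | 1.055 | 0.393 | 0.032 | 93.7% |
| 4 | 5.5 | 0.10 | 1.45 | 1.107 | 0.412 | 0.038 | 92.3% |

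A simulation with 22 teams per arm, a true difference of −0.5, a pooled t interval and 200,000 trials per setting agrees. For ICC 0.05 and 0.10 it gives errors of 0.039 and 0.056 with two facilitators, and 0.032 and 0.039 with four.

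A correct standard error also costs power. By the normal approximation, with a true difference of zero and the two-sided 95% interval, power falls from 0.749 without clustering to 0.653 (k = 2, ICC 0.05) or 0.575 (k = 2, ICC 0.10).

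**Step 3. Site.** With an even split, the difference in site mix between unstratified arms has SD √(2 × 0.25/22) = 0.15, or 15 percentage points. A 0.3-point site difference adds 0.3² × 0.25 = 0.0225 to the variance. Relative to 0.63² = 0.397 that is 5.7%, on posttest data alone.

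The planned model adjusts for the pretest, which absorbs much of a site difference present at both visits. Write s² = 0.397, v = 0.0225 and ρ for the within-site correlation, with equal variances at both visits. The residual variance without site is (s² + v) − (ρs² + v)²/(s² + v); with site it is s²(1 − ρ²). The ratio gives an excess of 2.9% at ρ = 0.3, 1.8% at 0.5 and 0.9% at 0.7.

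**Step 4. Does omitting site narrow the interval?** No. In a posttest-only simulation with a large site effect of 0.8 SD, the model without site keeps its error at 0.025 and its coverage at 95.1%. Its mean interval width is 0.823, against 0.773 with site: wider, not narrower. Nor does adding site repair the facilitator problem. In the same simulations, with k = 2 and ICC 0.10, the error is 0.054 with site and 0.051 without.

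**The case against.** - **A reader might infer that omitting site and facilitator together makes the interval too narrow.** The site half of that is wrong, as step 4 shows. Unstratified randomization keeps the analysis valid without site, and the article already discloses that chance imbalance remains possible.
- **A reader might take it as documented that teams share debriefers.** It is not; the article refers only to a medical doctor. With 22 teams in the arm sharing is very probable, but it is an inference.
- **The ICCs are assumed.** Formal training and a common debriefing framework argue for a small value, and at 0.01 with two facilitators the error is 2.8%. This stands, and is why the size can only be given as a range.
- **The inflation depends on the target of inference.** If the conclusion is confined to the facilitators actually used, differences between them are part of the comparator and the planned interval is not invalid on this account. This also stands, although the Discussion reads more broadly.
- **The sample size uses a one-sided alpha of 5%, and only the worst case above exceeds it.** True, but the decision rule uses the two-sided 95% interval, so 2.5% is the level the plan claims. At a nominal 5% the same settings would give about 5.9–9.0%.
- **A condensed article leaves details to other documents.** That covers the missing number of facilitators, which is not the fault raised here. It does not cover the model, whose terms the article lists in full.
- **A facilitator random effect may not be estimable.** With one facilitator the effect is fully confounded with arm. With one per site it is aliased with site within the arm. With two, the variance rests on about one degree of freedom. This stands, and the fix needs a fallback.

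**Conclusion.** The point holds in two separate parts.

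**Site.** Leaving it out is a modest loss of precision and of protection against chance imbalance. For an assumed 0.3-point difference it is about 6% of variance on posttest data alone and about 1–3% after the planned baseline adjustment. It is not an error in the interval.

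**Facilitator.** If facilitators differ, and if the conclusion is meant to apply beyond those used, the planned interval is too narrow in the direction that favours declaring non-inferiority. With 2–4 facilitators and an ICC of 0.05–0.10, the one-sided error is about 3.2–5.5% instead of 2.5%, and coverage is about 89–94%. At ICC 0.01 the effect is negligible; at zero there is none. The number of facilitators and the ICC are assumptions. The calculation uses the two-sample approximation behind the plan's own sample size; baseline adjustment would change the absolute widths but not the direction.

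This is worth changing because the change is cheap and the error is not conservative. It does not show that the primary analysis is invalid.

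**What to change.** 1. Add site as a fixed covariate in the team-level and individual-level models. This is for precision and does not address facilitator clustering.
2. Log the facilitator for every team in the facilitator-guided arm. Data collection has already begun, so recover this from session records for teams already trained. Report the number of facilitators, their sites and the teams per facilitator.
3. Pre-specify one sensitivity analysis of the primary outcome: a facilitator random effect at posttest in the facilitator-guided arm only, with small-sample degrees of freedom. Report whether the non-inferiority conclusion holds with and without it. Facilitator identity reveals the arm, so run it after the blinded primary analysis.
4. Fallback: if facilitators are too few or aliased with site, recompute the interval over a stated range of assumed facilitator ICCs, using the formula in step 2. If there is only one facilitator, limit the conclusion to that facilitator.

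The cost is one degree of freedom for site, one logged field and one extra analysis. The facilitator variance will be imprecise, which is why this is a sensitivity analysis and the primary decision rule stays as it is.
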